### Secondary outcomes

Secondary outcomes will be assessed as candidate primary outcomes and used in providing effect size estimates for power calculations for future trials.Suitability of the candidate primary outcomes will be defined by:Acceptability (feedback on burden and clarity from exit questionnaires),Variability (sufficient spread in scores without floor/ceiling effects),Sensitivity to change, defined as evidence of within-group and between-group score changes over time in the expected direction (mean change scores with 95% CIs).Descriptive statistics will be aggregated by assigned condition and presented in tables, including means, medians, standard deviations, variances, range, 95% confidence intervals and levels of missingness.

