**Methods:**

This study is a double-blind, parallel-group feasibility randomised controlled trial recruiting 60 adults meeting inclusion criteria for clinical depression. Participants are allocated 1:1 either to the CURED intervention or a neutral CBM-I control matched for format, length, and delivery, though differing in content. Both arms involve six weekly sessions delivered via mailed pen-and-paper booklets, with remote researcher support to ensure fidelity, and assessment at baseline, post-treatment (6 weeks) and 12-week follow-up. Primary outcomes are feasibility (response, recruitment, eligibility, randomisation, retention, weekly assessment completion, adherence, and randomisation rates); acceptability (Credibility and Expectancy Questionnaire, Exit Questionnaire, and qualitative interviews); integrity of blinding; and safety (adverse and serious adverse events). Secondary outcomes include interpretation bias, depressive and anxiety symptoms, cognitive content and processes, and psychosocial functioning. Analyses will summarise feasibility metrics descriptively and provide variance estimates to inform sample size calculations and primary outcome selection for a future definitive trial.

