#### Secondary outcomes

The secondary outcomes will assess the suitability of candidate clinical and cognitive measures as potential primary outcomes in a future definitive RCT. This includes evaluating their sensitivity to change over time and estimating between-group effect sizes (with 95% confidence intervals) to inform sample size calculations (please see Table 2 for the full assessment schedule).

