### Sample size {19}

As this is a feasibility trial, formal power analysis was not appropriate. Consistent with recommendations that feasibility studies include approximately 25–35 participants per arm [36–38], we set our target sample size at 30 participants per arm (60 participants in total).

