#### Primary outcomes

Feasibility metricsResponse rate: N, percent, who progressed from initial referral to first direct contact.Recruitment rate: N, percent, consenting.Eligibility rate: N, percent, eligible (meeting inclusion and exclusion criteria after screening).Randomisation rate: n, percent, randomised overall and per month against the target of 60 total, five per month.Retention: N, percent, providing data at post-treatment and 12-week follow-up.Assessment completion: N, percent, completion overall and per week throughout the intervention period.Adherence: mean (SD) number of sessions completed out of six, and percentage completing ≥ 80 % (≥ 5/6).Acceptability metricsCredibility and Expectancy Questionnaire: mean (SD) scores summarised by group at baseline and post-treatment.Exit Questionnaire: mean (SD) Likert-scale ratings on overall experience, manageability, and likelihood of future use at week 12.Qualitative Interviews: with a purposive subsample (*n* = 8, intervention arm) varying in gender, depression severity, age, and ethnicity, analysed thematically to explore acceptability, barriers, facilitators, and delivery preferences.Integrity of blindingSuccess of randomisation and concealment summarised descriptively.Percentage of unblindings reported as protocol violationsAnalysis of participants’ guesses of allocation at 12-week follow-up.SafetyFrequencies, severities, and relatedness of all AEs/SAEs by arm will be presented descriptively and tabulated.Qualitative content analysis of AE reports will identify common categories and potential risk factors.

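### Between-group effects from about 30 per arm are to screen candidate primary outcomes and feed the next trial's power calculation, which is likely to inflate the effect and underpower that trial

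*Protocol article*

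**What the plan says.** Two places in the protocol article give between-group effects a role in sizing the definitive trial. Under Outcomes {16}, Secondary outcomes, the work includes "estimating between-group effect sizes (with 95% confidence intervals) to inform sample size calculations". Under Statistical methods {27a}, Secondary outcomes: "Secondary outcomes will be assessed as candidate primary outcomes and used in providing effect size estimates for power calculations for future trials".

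The {27a} text then defines suitability as a primary outcome by three criteria: acceptability, variability without floor or ceiling effects, and sensitivity to change. The third is defined as "evidence of within-group and between-group score changes over time in the expected direction", shown as mean change scores with 95% confidence intervals.

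The abstract describes the output differently. Analyses will "provide variance estimates to inform sample size calculations and primary outcome selection for a future definitive trial". Objectives {10} likewise lists descriptive data and variance estimates for future trials, and an assessment of candidate measures, but not effect sizes.

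Sample size {19} sets 30 per arm from a rule of thumb and says that "formal power analysis was not appropriate". Section {5} says the statistical analysis plan is integrated in sections {27a–d} and that no separate one will be published.

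**The concern.** A feasibility sample of this size can estimate a standard deviation usefully. It cannot estimate a treatment effect usefully, because the interval is wide enough to cover both no effect and a large one. Two problems follow.

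First, if an outcome qualifies partly because its between-group difference points the right way, the differences that survive are on average too large. Feeding a survivor into a power calculation makes the next trial too small.

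Second, a good outcome can fail the criterion by chance.

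The Discussion justifies the study as protection against arbitrary outcome selection and sample size estimates, so the point touches its stated purpose. It does not touch this trial's own primary results, which are feasibility, acceptability, blinding and safety.

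**Working it through.** **The plan's own figure.** 2 × 30 = 60, and 30 lies in the cited range of 25 to 35 per arm. No alpha, power, effect size, SD or dropout rate is given, so there is no power calculation to reproduce.

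**Inputs.** From the article: 30 per arm, 1:1 allocation. Assumed here: true standardised difference d of 0.2, 0.3 or 0.5; 24 per arm as a 20% loss case (30 × 0.8); next trial at two-sided 5% and 80% power.

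**1. Precision.** SE(d) = √(2/n + d²/(4n)). For d = 0.3:
- n = 30: √(0.0667 + 0.0008) = 0.260, so the 95% half-width is 1.96 × 0.260 = 0.51.
- n = 24: √(0.0833 + 0.0009) = 0.290, so the half-width is 0.57.

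An observed 0.3 at 30 per arm is compatible with about −0.2 to 0.8.

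**2. Failing the direction criterion by chance.** P(wrong sign) = Φ(−d/√(2/n)). For d = 0.3:
- n = 30: Φ(−0.3/0.258) = Φ(−1.16), about 12%.
- n = 24: Φ(−0.3/0.289) = Φ(−1.04), about 15%.

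**3. Inflation from a direction-only screen.** With s = √(2/n) and z = d/s, the mean of the estimates that are kept is d + s·φ(z)/Φ(z). For d = 0.3, n = 30: 0.3 + 0.258 × 0.203/0.877 = 0.36. Without a screen, simulated mean estimates were 0.199, 0.302 and 0.499 for true values 0.2, 0.3 and 0.5. The bias therefore comes from selection, not from the small sample as such.

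**4. Consequence for the next trial.** Planned size per arm is N = 2(1.96 + 0.842)²/g² = 15.7/g², where g is the retained estimate. True power is Φ(d√(N/2) − 1.96). Averaged over simulated feasibility trials with 30 per arm, one outcome, kept only if g > 0:

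| True d | Mean retained g | Inflation | N per arm needed | Mean true power | Chance power is below 80% |
|---|---|---|---|---|---|
| 0.2 | 0.30 | 49% | 393 | 59% | 64% |
| 0.3 | 0.36 | 20% | 175 | 67% | 57% |
| 0.5 | 0.52 | 3% | 63 | 75% | 50% |

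At 24 per arm, mean true power is 56%, 65% and 74%. In the d = 0.5 row there is almost no inflation, yet mean power is still below 80%. That loss comes from imprecision: the power lost when g is too high exceeds the power gained when it is too low.

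**5. What the trial can supply.** The 80% one-sided upper limit for the pooled SD is √(df/χ²₀.₂₀,df) times the estimate: 1.09 with 58 df (30 per arm) and 1.10 with 46 df (24 per arm). It raises the required size by 1.09² = 1.19, so 175 per arm at a target d of 0.3 becomes about 208.

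**The case against.** The strongest reply is that the article fixes very little. It says the effect sizes will inform the calculation and attaches 95% confidence intervals. It does not say the point estimate will be used alone, and it does not exclude a minimal important difference. The target difference will be set in the definitive trial's own protocol. Between-group direction is only part of one criterion in three. A single outcome named in advance would give an unbiased estimate. The {27a} text also promises SDs, variances, ranges and missingness, and retention is a primary outcome, so most of what a sound calculation needs is already planned.

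All of that stands, and it limits the claim to what is likely. It does not remove the point. Two sections name effect sizes as an input to power, direction is a stated criterion, and the text gives no external target and no allowance for imprecision beyond reporting intervals.

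Three stronger readings are tempting but unsupported:
- **The outcome with the largest effect will be chosen.** For the largest of six candidates with true d = 0.3 (assumed correlation 0.5 to 0.7, 24 to 30 per arm), the expected estimate would be about 0.48 to 0.56. The article has no ranking and no largest-effect rule, so this is a worst case. The count of six is also doubtful: Table 2 as printed shows no baseline GAD-7, so that scale has no change score.
- **Effect sizes replace variance estimates.** They are added to them.
- **Evidence of change means an interval excluding zero.** Section {27a} rules out formal hypothesis testing, so this should not be read in.

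**Conclusion.** The point holds as a matter of likelihood. The plan lets the same imprecise contrast help screen outcomes and feed the next power calculation, and its methods go further than its abstract and objectives. On the mildest reading (direction-only screen, 30 per arm, next trial sized for 80% on the point estimate), mean true power is about 67% if the true difference is 0.3, and between 59% and 75% across 0.2 to 0.5. A candidate with a true difference of 0.3 has a 12–15% chance of failing the direction criterion by chance.

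These figures rest on assumed true effects, an assumed 20% loss for the 24-per-arm case, and use of the point estimate, none of which the article states. A reader might infer that an inflated effect and an underpowered trial are certain. They are not: at a true difference of 0.5 the inflation is 3% and falling short of 80% power is about an even chance.

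**What to change.** In Outcomes {16} and Statistical methods {27a}, Secondary outcomes:

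- State that the definitive trial's sample size will use a target difference justified outside this trial, such as a minimal important difference. MCID is in the abbreviation list but is not used in the text. Combine it with this trial's SD at an upper confidence limit (for example the 80% one-sided limit, about 1.09–1.10 times the estimate), the baseline-to-follow-up correlation, and retention.
- Remove between-group direction from the suitability criteria. Judge sensitivity to change on change pooled over arms. The global rating of change can anchor this at 6 weeks only, since Table 2 schedules it at no other visit.
- Keep acceptability and floor/ceiling effects as criteria, and add completeness.
- Report between-group differences with 95% confidence intervals as descriptive only, in line with the abstract and objectives.

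The cost is wording in two sections and no new data. The downside is small: the next trial may be planned larger, and this trial gives less direct guidance on effect size.

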### Sequence generation: type of randomisation {21b}

Stratified block randomisation will be used to allocate participants to intervention or control arms using an excel spreadsheet. Stratification will be based on sex at birth (male/female) and number of previous depressive episodes (0/1/2 +).

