#### Who will be included in each analysis {27b}

All available data will be included in the final aggregations, with sensitivity analysis excluding certain characteristics (e.g. low adherence, withdrawal, starting therapy or medication) where applicable.

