#### Protocol and statistical analysis plan {5}

A statistical analysis plan (SAP) is integrated within this protocol (see Sections {27a–d}). No separate standalone SAP will be published, as is appropriate for a feasibility trial with primarily descriptive statistical methods. Should amendments be required, these will be documented and reported in academic publications in accordance with CONSORT and SPIRIT guidelines.

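### Between-group effect sizes are promised for planning the next trial, but the only between-group quantity the plan names is the unadjusted mean change score, with no use of baseline score or strata

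*Protocol article*

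**What the plan says.** Section {16} of the protocol article (Outcomes, Secondary outcomes) gives the secondary measures two jobs. One is to show sensitivity to change. The other is "estimating between-group effect sizes (with 95% confidence intervals) to inform sample size calculations". No estimator is named there.

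Section {27a} (Secondary outcomes) repeats that these measures will supply effect sizes for future power calculations. It then defines sensitivity to change as "evidence of within-group and between-group score changes over time in the expected direction (mean change scores with 95% CIs". It also promises tables by arm that include means, SDs, variances and 95% confidence intervals. Section {27b} adds that "All available data will be included in the final aggregations".

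Under {21b}, "Stratification will be based on sex at birth (male/female) and number of previous depressive episodes" (three levels of the latter). Neither factor reappears in {27a} to {27d}, and nothing there mentions adjustment for baseline score.

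Section {5} states that the analysis plan is contained in {27a–d}, and that "No separate standalone SAP will be published".

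**The concern.** Variance estimates for future trials are a listed objective ({10}), and {27a} sets aside hypothesis tests in favour of description and estimation. The choice of estimator therefore decides how good a stated deliverable is.

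The one between-group summary named is a simple difference in mean change. Change scores subtract the whole baseline value, although follow-up usually depends on baseline with a slope below 1. This over-correction has two effects. The interval is wider than it need be, and with 30 per arm a chance difference at baseline carries through into the estimate with the opposite sign.

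For planning, a change-score SD gives a larger sample size than a definitive trial would need if it adjusted for baseline.

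**Working it through.** **The plan's own figure.** The target is 2 × 30 = 60, chosen from a recommended range of 25 to 35 per arm. Section {19} gives no power calculation, so there is no formula to reproduce and no SD, correlation or effect size to draw on.

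**Inputs.** From the documents: 30 per arm, 1:1 allocation, 95% intervals, six strata (2 × 3). Assumed: correlation r from 0.3 to 0.8, equal SD at baseline and follow-up (set to 1), no dropout.

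**Variances.**
- Change score: 2(1 − r)
- Follow-up adjusted for baseline: 1 − r²
- Ratio: 2/(1 + r), which is 1.54, 1.33, 1.18 and 1.11 at r = 0.3, 0.5, 0.7 and 0.8

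**Half-widths, 30 per arm.**
- Change score: t(58) × √[2(1 − r) × 2/30]
- Adjusted: t(57) × √[(1 − r²) × 2/30 × (1 + 1/56)]

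At r = 0.5 these are 2.002 × √0.0667 = 0.517 and 2.002 × √0.0509 = 0.452.

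| r | Change score | Baseline-adjusted | Excess width | Excess if strata also adjusted |
|---|---|---|---|---|
| 0.3 | 0.612 | 0.498 | 23% | 19% |
| 0.5 | 0.517 | 0.452 | 14% | 11% |
| 0.7 | 0.400 | 0.373 | 7.5% | 4% |
| 0.8 | 0.327 | 0.313 | 4% | 1.5% |

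The last column adds three parameters for the strata and assumes they have no prognostic value. A plain comparison of follow-up scores has half-width 0.517, so below r = 0.5 the change score does worse than ignoring baseline altogether.

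**Chance imbalance.** The standard error of the baseline difference is √(2/30) = 0.258 SD. An imbalance of that size shifts the change-score difference by (1 − r) × 0.258, which is 0.13 SD at r = 0.5 and 0.08 SD at r = 0.7. In 4,000 simulated trials the correlation with baseline imbalance was −0.48 and −0.38 for change scores, and 0.03 and 0.00 for the adjusted estimate. Both averaged close to the true value of zero.

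**Planning.** For an assumed 0.4 SD difference, 80% power and two-sided 5%, the number per arm from the change-score SD against the adjusted SD is 138 against 90 (r = 0.3), 99 against 74 (r = 0.5) and 59 against 51 (r = 0.7).

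**Unequal SDs.** With baseline SD s0 and follow-up SD s1, the change-score variance exceeds the adjusted variance by (s0 − r·s1)². This vanishes when s0/s1 = r. For an assumed s0/s1 of 0.7 to 0.8, the variance ratio is (k² + 1 − 2rk)/(1 − r²) with k = s0/s1:
- r = 0.3: 1.07/0.91 = 1.18 to 1.16/0.91 = 1.27
- r = 0.5: 0.79/0.75 = 1.05 to 0.84/0.75 = 1.12
- r = 0.7: 0.51/0.51 = 1.00 to 0.52/0.51 = 1.02

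**The case against.** A reader might infer that the promised effect sizes will be computed from raw change scores. The text does not say so. The change-score wording defines sensitivity to change, {16} lists that separately from effect-size estimation, and no estimator is given for the latter. What stands is narrower: the only between-group quantity named is unadjusted.

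A reader might also infer that the variance passed to the next trial will be wrong. That does not follow. A change-score variance is valid for a trial analysed on change scores and conservative for one that adjusts for baseline. SDs are tabulated too, so the correlation can be recovered as r = (s0² + s1² − s_change²)/(2·s0·s1) if all three SDs come from the same participants. This only partly answers the point. A change-score SD is not promised by name, and using all available data means that, with dropout, the visits may rest on different people.

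The size of the gain is open to challenge as well. Entry requires BDI-II of at least 15, which cuts off the lower end at baseline, so a smaller baseline SD is plausible for the depression measures. In that case the gain shrinks, as the unequal-SD figures show. This objection stands.

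The strata matter little. Leaving out prognostic strata usually makes intervals somewhat conservative, and adjusting for non-prognostic ones costs about 3% in width. Finally, the article condenses a fuller protocol that is not shown. However, {5} places the analysis plan in these sections, so the document does not point to a model elsewhere.

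**Conclusion.** The point holds as a modest, nearly free improvement to the estimation plan. The effect-size estimator is not fixed, and the one between-group summary named uses neither baseline nor strata. With 30 per arm, equal SDs and r of 0.3 to 0.7, that summary gives intervals about 23% to 7.5% wider than baseline adjustment and moves with chance imbalance. Both conditions are assumptions, and the advantage could be close to nil if the baseline SD is clearly below the follow-up SD.

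It would be wrong to read this as bias, since both estimators are unbiased over randomisations. Nor does it touch the feasibility, acceptability, blinding or safety conclusions, or the target of 60, because no hypothesis test is planned.

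**What to change.** Add to {27a}, and cross-refer from {16}:

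- For each secondary measure with a baseline, report the between-arm difference at 6 and at 12 weeks, adjusted for baseline score and, if wanted, for sex at birth and previous episodes. Give the 95% interval and no p-value.
- Report the residual SD and the baseline-to-follow-up correlation for planning.
- Keep mean change scores by arm as description.

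As Table 2 reads in the text at hand, the GAD-7 is collected only at 6 and 12 weeks. It would then allow neither a change score nor adjustment for its own baseline, and the plan should say how it is to be summarised.

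The cost is a few sentences and a little programming, with no new data. Section {5} provides for documented amendments and recruitment is expected to run to 1 July 2026, so the wording can be settled before outcomes are compared by arm.

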#### Who will be included in each analysis {27b}

All available data will be included in the final aggregations, with sensitivity analysis excluding certain characteristics (e.g. low adherence, withdrawal, starting therapy or medication) where applicable.

#### How missing data will be handled in the analysis {27c}

Missingness will be reported for each variable, following CONSORT guidelines, including reasons for loss to follow-up, where known. We do not anticipate differential attrition between arms, as participants will be unaware of their allocation, though this will still be assessed by examining completion rates of assessments and assigned sessions across arms separately. To examine potential bias, baseline characteristics will be compared between participants with complete versus missing follow-up data within each arm. Missingness will also be summarised both as proportions per variable and graphically (ranking variables from most to least complete). Predictors of missingness will be examined across the entire sample and by arm to inform missing at random assumptions in a full trial.

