	**Screening (-T**_**1**_** to T**_**0**_**)**	**Baseline (T**_**0**_**)**	**Interim assessments (T**_**i1-5)**_^**c**^	**6-week follow-up assessment **(**T**_**1**_**)**	**12-week follow-up (T**_**2**_**)**
Enrolment					
* Informed consent procedures*					
Participant information sheet	X				
Consent form	X				
*Eligibility check*					
Inclusion/exclusion criteria checklist	X				
Capacity assessment tool (if applicable)	X				
M.I.N.I. screening tool	X				
Beck depression inventory–II (BDI-II)	X	X		X	X
Intervention/comparator					
CURED (intervention)					
Neutral CBM-I (control)					
Assessment instruments					
*Sociodemographic information*					
Socio-demographic questionnaire		X			
*Clinical symptoms*					
M.I.N.I. MDD module		X			
Patient Health Questionnaire-9 (PHQ-9)		X	X	X	X
Beck Depression Inventory-II (BDI-II)		X		X	X
Depression, Anxiety, and Stress Scale-21 (DASS-21)		X		X	X
Generalized Anxiety Disorder-7 (GAD-7)				X	X
*Interpretation bias*					
Scrambled Sentence Task (SST)		X C/bal^b^	X C/bal	X C/bal	X C/bal
Similarity Rating Test (SRT)		X C/bal		X C/bal	X C/bal
*Cognitive content*					
Automatic Thought Questionnaire-Revised (ATQ-R)		X		X	X
Cognitive Distortions Scale (CDS)		X		X	X
*Prospective Imagery Task (PIT)*		X		X	X
*Cognitive process*					
Repetitive Thinking Questionnaire (RTQ-10)		X		X	X
Interpretation Inflexibility Task (IIT)		X		X	

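### Change in PHQ-9 and SST is estimated only from people with a follow-up value, and the weekly values already collected are assigned neither to that estimate nor to the attrition check

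*Protocol article*

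**What the plan says.** Section {5} of the protocol article places the statistical analysis plan in sections {27a–d} and says that no standalone plan will be published. These sections can therefore be read as the analysis plan.

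- **Estimating change.** Under Secondary outcomes in {27a}, a candidate outcome's sensitivity to change is judged within and between groups by "mean change scores with 95% CIs". The same section uses the secondary outcomes to supply effect sizes for future power calculations.
- **Who is included.** Section {27b} takes all available data. Its sensitivity analyses only remove people, such as poor adherers, those who withdraw and those who begin other treatment.
- **Checking for attrition bias.** In {27c}, the check introduced as examining potential bias is that "baseline characteristics will be compared between participants with complete versus missing follow-up data within each arm". The section also plans to report missingness "including reasons for loss to follow-up, where known", to look for differential attrition by "examining completion rates of assessments and assigned sessions across arms separately", and adds: "Predictors of missingness will be examined across the entire sample and by arm to inform missing at random assumptions in a full trial".
- **Weekly data.** Table 2 schedules PHQ-9 and SST at baseline, at the five interim assessments, and at 6 and 12 weeks. Footnote c says that an interim assessment is done only once that week's session has been completed.

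**The concern.** A change score needs a follow-up value, so the mean change describes only the people still being assessed. It is unbiased for everyone randomised only if dropout is unrelated to course. The protocol makes such a link plausible. Section {15b} allows discontinuation for mood worsening judged related to study procedures, and section {17} names temporary distress from the intervention content as the main potential harm.

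A baseline comparison is a weak guide to this kind of loss, because someone who worsens after randomisation can look ordinary at baseline. The weekly PHQ-9 and SST values are the information closest to the event. They are collected, but no section says that they will enter the change estimate or the bias check.

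Three outputs of the trial are at stake: the choice of a candidate primary outcome, the effect sizes passed to the next sample size calculation, and the missingness work meant "to inform missing at random assumptions in a full trial".

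**Working it through.** The plan states no figure for this point, so there is none to reproduce. The target of 60 is a rule-of-thumb size (2 × 30 = 60) without a power calculation.

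**Inputs.** From the protocol: 30 per arm and five interim assessments. Assumed, because the protocol gives none of them: dropout 10–30%; SD of PHQ-9 change σ = 5 points; true mean change −3; correlation ρ of interim change with week-6 change 0.5–0.7; odds ratio (OR) for dropout of 1 to 3 per SD of interim worsening.

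**Size of the bias.** Let a be the standardised interim change, with positive values meaning worse. Then week-6 change = −3 + σ(ρa + √(1−ρ²)e), where e is independent noise, and the log-odds of dropout are linear in a. The bias of the available-case mean is σ × ρ × E(a | stayed). With 500,000 simulated people per scenario, improvement is overstated by the following number of PHQ-9 points (ρ = 0.5 to ρ = 0.7):

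| Dropout | OR 1 | OR 1.5 | OR 2 | OR 3 |
|---|---|---|---|---|
| 10% | 0.00 | 0.10–0.14 | 0.16–0.24 | 0.24–0.34 |
| 20% | within 0.01 | 0.19–0.28 | 0.33–0.45 | 0.46–0.65 |
| 30% | within 0.01 | 0.30–0.41 | 0.47–0.68 | 0.67–0.95 |

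The formula gives a hand check at 20% dropout and OR 2. Here −0.33/(5 × 0.5) = −0.13 and −0.45/(5 × 0.7) = −0.13, so both correlations imply the same shift among stayers, as they should. In SD units the range is 0.10/5 = 0.02 to 0.95/5 = 0.19. Regressing on the interim value returned the true mean, to within 0.01, in every scenario.

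**A second model.** Weekly trajectories were simulated with PHQ-9 mean 14, person SD 4, slope SD 0.7 per week, residual SD 2.3, 22–23% dropout, and log-odds of leaving 0.15 or 0.30 per point of worsening.

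- True change was −3.0 and completers showed −3.49 and −3.88, an overstatement of about 0.5 and 0.9 points.
- Leavers were 0.19–0.32 SD milder than stayers at baseline but 0.61–1.09 SD worse on change to the last weekly value.
- The dropout link is strong. The SD of change by week 5 is √((5 × 0.7)² + 2 × 2.3²) = √22.83 ≈ 4.8, so the odds ratios per SD are about exp(0.15 × 4.8) ≈ 2 and exp(0.30 × 4.8) ≈ 4.

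**Between arms.** Equal dropout with an equal link cancels. Dropout of 10% against 30%, both at OR 2 and ρ = 0.7, leaves 0.68 − 0.24 = 0.44 points. A link in one arm only leaves that arm's whole bias.

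**Precision.** For leavers against stayers, the 95% half-width of a standardised difference at 20% loss is 1.96√(1/6 + 1/24) = 0.89 within an arm and 1.96√(1/12 + 1/48) = 0.63 pooled. For mean change with 24 observed per arm, it is 1.96 × 5/√24 = 2.0 points within an arm and 1.96 × 5 × √(2/24) = 2.8 points between arms.

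**The case against.** A reader might infer that the plan looks only at baseline characteristics and would therefore miss dropout after worsening. The text does not support that. Section {27c} plans predictors of missingness across the whole sample and by arm without restricting them to baseline variables. It ties the missing-at-random question to that analysis, not to the within-arm baseline comparison. Reasons for loss, completion rates by arm, the mood check at the week 3 call and the adverse event tables could also bring worsening to light. Under {25b}, someone who stops sessions may still give outcome data. What remains is that the predictors are unnamed.

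The weekly values are also not excluded. PHQ-9 and SST are secondary outcomes, and their weekly scores may well appear in the descriptive tables. That still leaves no estimate of change that uses them.

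The size is assumed throughout, and it is modest against half-widths of 2.0 and 2.8 points. That limits the weight of the point, but an available-case bias does not shrink as the sample grows, and these estimates are meant to be carried forward.

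The adjusted estimates recover the truth because simulated dropout depends on observed weekly scores. Under footnote c of Table 2, someone who worsens and then stops sessions leaves no weekly record of it. This objection stands and limits what the remedy can claim.

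Finally, the plan is descriptive and tests no hypothesis. A model-based estimate with a confidence interval is still estimation, so it fits {27a}.

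**Conclusion.** The point holds in a limited form. The planned change estimates for PHQ-9 and SST use only people with a follow-up value. The sensitivity analyses only remove more people, the one check labelled as a bias check is on baseline characteristics within arm, and the predictors of missingness are unnamed. No section puts the weekly values to use for either purpose.

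If dropout follows interim worsening, improvement is overstated by about 0.1–0.95 PHQ-9 points (0.02–0.19 SD of change) under the assumed ranges. No size was worked out for SST.

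It would go too far to say that improvement will be overstated, or that the comparison of arms is biased. The protocol gives no dropout rate or mechanism. The bias is zero if dropout is unrelated to course, and the between-arm contrast is affected only if the dropout rate or its link to worsening differs by arm. This is a worthwhile, inexpensive improvement to estimates that feed the definitive trial, not the correction of an invalid analysis.

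**What to change.** 1. In {27a}, for PHQ-9 and SST, report a likelihood-based repeated-measures estimate beside the available-case change score. It should give the 6-week within-arm change and the between-arm contrast, with 95% CIs, and include the baseline and weekly values.
2. In {27c}, name change from baseline to the last observed weekly PHQ-9, and the number of sessions completed, among the predictors of missingness already planned for the whole sample and by arm.
3. In {27c}, state that finding no predictor will not be read as support for missing at random. The half-widths of 0.63 to 0.89 SD show why.

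The cost is one extra model for two measures and a few sentences of text, with no new data. With seven time points (baseline, five weekly, week 6) an unstructured covariance has 7 × 8/2 = 28 parameters, so a simpler fallback structure should be named in advance. The limit should be stated with the results: weekly values exist only after a completed session, so worsening after the last session is not captured and the bias is reduced, not eliminated.
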